## 5.2 SUPPORTIVE THERAPIES

All occurrences of late-onset diarrhea should be treated aggressively with loperamide (imodium) or atropine sulfate / diphenoxylate hydrochloride (lomotil; lomotil can be substitute for loperamide in all of the below sections). Since uncontrolled diarrhea may lead to hospitalization for dehydration, patients should be instructed to maintain proper hydration. If warranted, patients should be given supplemental fluids (intravenously, if indicated) at any signs of dehydration (clinical signs plus weight loss of  $\geq 1$  kg at a particular weekly visit).

For patients entered into dose levels 2-4, atropine per institutional standards, may be given to treat acute-onset diarrhea from irinotecan. All patients will be instructed to begin taking loperamide at the earliest signs of diarrhea (i.e., first poorly formed or loose stool, first episode of an increase of two or more bowel movements in one day). Loperamide should be taken in the following manner: 4 mg at the first onset of diarrhea, then 2 mg every 2 hours around-the-clock until diarrhea-free for at least 12 hours. Patients may take loperamide 4 mg every 4 hours during the night. If patients require more than 16 mg of loperamide per day, alternative antidiarrheal medications should be institution with consideration of evaluation of the patient.

Antiemetics should be prescribed by the treating physician as clinically indicated if a patient develops nausea and/or vomiting. Prophylactic antiemetics prior to IV therapies will be determined by treating clinicians.

Prophylactic use of a colony-stimulating factor (G-CSF or GM-CSF) is permitted after a first event of grade 3 or 4 neutropenia, as discretion of treating clinician. Use of erythropoietin (including Procrit and Aranesp) for treatment or disease-related anemia is permitted.

Supplementation of electrolytes (potassium, magnesium) is permitted and recommended to maintain serum potassium at least 3.0 mmol/L and serum magnesium at least 1.8 mg/dL or within institutional normal limits. Study agents may be administered while repletion occurs.

There is no standard, known, or established treatment proven effective for drug-related skin rashes or changes due to cetuximab or ZD6474. Most commonly, a pustular rash has been observed, which frequently improves with same dose of uninterrupted EGFR inhibitor therapy. The need for oral or topical antibiotics is a clinical decision of the investigator and should be preceded by a culture of affected areas and, if indicated, a dermatology consultation (though oral antibiotics in Appendix A are prohibited, topical antibiotics [even listed in Appendix A] are permitted). Systemic or topical steroids are discouraged for the treatment of skin toxicities. Treatment with topical erythromycin, topical tetracycline, topical clindamycin, topical silver sulfadiazine, and diphenhydramine is allowed at the discretion of the treating clinician.

The administration of radiation is not permitted and patients requiring radiotherapy will be removed from the study.

Concomitant use of the known potent inducers of CYP3A4: rifampicin, phenytoin, carbamazepine, barbiturates and St. John's Wort are not allowed within 2 weeks of study or during the study.

Concomitant use of medications generally accepted as having a risk of causing Torsades de Pointes (see Appendix A, List 1) are allowed at the time of study entry (if there is no appropriate alternate medication). Patients who are receiving drugs that may induce Torsades de Pointes, must have an additional ECG obtained 4-8 hours after the first dose of ZD6474.

Screening QTc must be <480 msec, or  $\leq 460$  msec for patients taking medications with known risk of Torsades de Pointes.

Baseline QTc (Bazett's) will be determined by the average of no less than 3 consecutive ECG's (within 5-10 minutes of each other).

ECG's will be repeated at weeks 1, 2, 4, 8 and 12; at discontinuation; and as clinically indicated.

If QTc prolongation occurs at one of the usual assessment times, or at any other time, the QTc will be re-evaluated with no less than 3 consecutive ECG's (within 5-10 minutes) of one another.

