### Protocol Clarifications (non-drug related e.g. eligibility criteria, study assessments)

**Protocol Section 4.2:** Patients must meet eligibility criteria of Potassium  $\geq 4$ . Once enrolled, there is no need to withhold ZD6474 if the K is 3.0-4.0. As with other toxicities, the cut-off for holding the dose would be CTCAE grade 3 toxicity (or K <3.0). The patient should continue to receive K supplementation.

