#### 7.1.5 Management of Gastrointestinal Toxicity

Nausea, vomiting, or both may be controlled with antiemetic therapy. Diarrhea should be treated with standard medications to avoid dose modification or interruption, if possible. Electrolyte supplementation with regular laboratory monitoring should be used, when appropriate, to maintain electrolytes within normal limits and prevent an increased risk of QTc prolongation. No dose modifications will be made because of grade 1 or 2 diarrhea. If grade 3 diarrhea develops, ZD6474 should be withheld until diarrhea resolves to grade 1 or below. Patients who are clinically unstable because of diarrhea or other intercurrent medical illness must be admitted and evaluated using telemetry, until clinically stable. Upon recovery, ZD474 may resume at a permanently reduced dose if patient developed diarrhea in the setting of optimal antidiarrheal management; else ZD6474 can be maintained at the same dose or reduced (at discretion of treating physician) and patient must be instructed as to optimal diarrhea management. If ZD6474 must be withheld for more than 3 weeks for resolution of diarrhea, the patient will withdrawn from study.

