#### 7.1.6 Management of Other Toxicity

If any other grade 3 or 4 toxicity that is not outlined elsewhere in Sections 7.1 develops and is deemed attributable to ZD6474, ZD6474 should be withheld until the toxicity resolves to grade 1 or below. Upon recovery, treatment may resume at a permanent reduced dose. If ZD6474 must be withheld for more than 3 weeks for resolution of toxicity, the patient will be withdrawn from study.

Patients who develop CTCAE grade 3 hypertension may continue on therapy if blood pressure is controlled on antihypertensive medication. If blood pressure cannot be stabilized with increased antihypertensive medication, study treatment must be discontinued and cannot be resumed until blood pressure is controlled to baseline level. Patients with CTCAE grade 4 hypertension should discontinue study treatment and cannot resume therapy until blood pressure is controlled to baseline level. If study treatment must be interrupted for more than 3 weeks to allow for toxicity to resolve, the patient's study participation will be discontinued.

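### Below a potassium of 3.0 the alert page holds ZD6474, while Section 5.2 lets study agents be given during repletion

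*Protocol*

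**What the plan says.** Four places in the protocol bear on potassium once a patient is on study.

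- **Alert page, Protocol Clarifications (filed under Section 4.2).** Entry requires potassium of at least 4. After enrolment, "there is no need to withhold ZD6474 if the K is 3.0-4.0", supplementation goes on, and "the cut-off for holding the dose would be CTCAE grade 3 toxicity (or K <3.0".
- **Section 5.2, Supportive Therapies.** Supplementation is permitted and recommended to "maintain serum potassium at least 3.0 mmol/L" and "serum magnesium at least 1.8 mg/dL or within institutional normal limits". The next sentence reads: "Study agents may be administered while repletion occurs". It names no potassium level below which it stops applying.
- **Section 7.1.5, Gastrointestinal Toxicity.** Supplementation with laboratory monitoring is to be used, where appropriate, "to maintain electrolytes within normal limits and prevent an increased risk of QTc prolongation". No potassium level for holding a dose is given.
- **Section 7.1.6, Other Toxicity.** For a grade 3 or 4 toxicity not covered elsewhere in Section 7.1 and attributed to ZD6474, "ZD6474 should be withheld until the toxicity resolves to grade 1 or below". Treatment may then resume at a permanently reduced dose.

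**The concern.** ZD6474 is one of the study agents. A clinician treating a patient whose potassium is below 3.0 finds a hold on the alert page and a permission to dose in Section 5.2. The hold is labelled as a clarification of the eligibility section, so someone working from the supportive-care or dose-modification sections would not meet it there.

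What is at stake is mainly safety and uniform conduct. Sections 1.7, 1.8 and 6.1 list QTc prolongation among the common adverse events of ZD6474, and Section 7.1.5 links electrolytes to that risk. The situation is foreseeable: Section 1.8 reports diarrhea in 55.4% of patients on ZD6474 monotherapy, and Section 6.2 names diarrhea as a major dose-limiting toxicity of irinotecan. With three centers expected, the same laboratory value could be handled differently from one to another.

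**Working it through.** No sample size, power or error rate is involved, so the check is a comparison of the texts by potassium range. The alert page gives no unit for its 3.0; I read it as mmol/L, as in Section 5.2.

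| Potassium on study | Alert page | Section 5.2 | Section 7.1.6 |
|---|---|---|---|
| 3.0 to 4.0 | ZD6474 need not be held; keep supplementing | Dosing allowed during repletion | Not reached, since the alert page pairs grade 3 with values below 3.0 |
| Below 3.0 | Hold ZD6474 | Dosing allowed during repletion, no lower limit | Withhold, if attributed to ZD6474 |

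**Step 1: the 3.0 to 4.0 band.** The alert page and Section 5.2 agree. Both continue dosing with supplementation.

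**Step 2: does the Section 5.2 permission reach below 3.0?** If its target is 3.0, repletion towards that target takes place below 3.0, so on its wording the permission covers the band in which the alert page holds the drug. If its target is instead the institutional normal range, repletion also covers higher values, but there is still no lower limit. The contradiction stands on either reading.

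**Step 3: does Section 7 settle it?** Not fully.
- Section 7.1.6 applies only when the event is attributed to ZD6474. The alert-page cut-off carries no such condition.
- The opening of Section 7 keeps patients on assigned doses through the DLT assessment period (28 days at dose level 1, 35 days at levels 2-4) unless a DLT occurs or the patient is withdrawn. It applies the modification guidelines to patients with a DLT in that period or with treatment-related toxicity after it.
- The summary table in Section 7.1.7 has no potassium entry, and the 3.0 cut-off appears nowhere in Section 7.1.

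**Step 4: the normal-limits clause.** In Section 5.2 the words "serum magnesium at least 1.8 mg/dL or within institutional normal limits" follow the potassium target in the same sentence. The clause may qualify both electrolytes or magnesium alone. If both, Section 5.2 names the same goal as Section 7.1.5 as an alternative to 3.0. If magnesium alone, the two sections word the potassium goal differently. The text does not decide which.

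**The case against.** The strongest reply is that a specific instruction governs a general one. Section 5.2 is about supportive care, its sentence is permissive and covers all study agents, and Section 5.1 sends the reader to Sections 6 and 7 for dose modifications. The alert page is a posted rule for ZD6474 and says that it follows the handling of other toxicities. Read together, the permission can be confined to 3.0 to 4.0. That is a reasonable reading, but the protocol states neither that limit nor that the alert page takes precedence. The revision history shows the protocol and alert page replaced together on 04/11/11, so posting order does not establish precedence.

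A reader might also infer a wider, three-way conflict over potassium levels: 4.0 at entry, normal limits in Section 7.1.5 and 3.0 in Section 5.2. The documents do not support that. The alert page expressly separates the entry level from on-study dosing. Section 7.1.5 is a supplementation goal under gastrointestinal toxicity, used where appropriate, with no rule for holding a dose. A minimum level and a normal-range goal can coexist, and Section 5.2 may itself name normal limits for potassium. Only the ambiguity in Step 4 remains from this.

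**Conclusion.** The point holds in a narrow form. For potassium below 3.0, the alert-page hold and the unlimited permission in Section 5.2 contradict each other as written, and Section 7.1 does not state the cut-off that would resolve this. The unclear scope of the normal-limits clause is secondary.

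The size cannot be given in patients, because the document reports no frequency of potassium below 3.0. No design quantity or statistical figure changes.

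A reader might infer that DLT counts, and so the MTD, would depend on which text a center follows. Section 3.2 does count grade 3 or greater cardiac toxicity, and grade III or higher nonhematological toxicity lasting more than a week (with listed exceptions), and cohorts are of 3. But the DLT definition does not refer to Section 5.2, and QTc prolongation has its own hold and withdrawal rules in Sections 7.1.2 and 7.1.3 whatever the potassium. An effect on DLT counts is possible but not shown.

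Accrual closed on May 18, 2010, so the correction serves patients still on treatment and the interpretation of events already recorded. The conclusion assumes that ZD6474 is among the study agents meant in Section 5.2 and that both texts use the same unit. It takes no view on which potassium rule is right.

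**What to change.** Reconcile the alert-page clarification, Section 5.2 and Section 7.1.6, so that Sections 5.2 and 7.1 carry one consistent instruction on ZD6474 when potassium is below 3.0. Make the Section 5.2 sentence on dosing during repletion agree with it. State which electrolytes the normal-limits clause covers, so that its relation to Section 7.1.5 is clear. The clinical team must choose the rule and the values. The cost is a wording amendment with its usual approval; no design or analysis element changes.

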## 6 DRUG FORMULATIONS AND SAFETY

### 6.1 ZD6474 (ZACTIMA)

#### Availability

ZD6474 will be supplied by AstraZeneca free of charge. AstraZeneca will pack tablets into high-density polyethylene (HDPE) bottles with child-resistant tamper-evident closures. Each bottle will be labeled with the statement: "Caution: New Drug - Limited by Federal (or USA) Law to Investigational Use". Instructions stating that the tablets are to be taken orally "as directed by your doctor" will be included. Information on the label will indicate the identity and quantity of tablets and storage conditions. Additional subject information will be identified as dictated by the protocol. The tablets should be stored in the original pack until use. For further information, investigators should refer to the investigational product label.

Tablets containing 100 mg of ZD6474 (ZACTIMA) are available and will be dispensed in a bottle containing 28 tablets, a quantity sufficient for 4 consecutive weeks of dosing.

#### Accountability

The trial treatment (ZD6474) must be used only as directed in the protocol. Records of overall dispensing and returns will be maintained separate from the case report forms (CRFs) recording the treatment dispensed to individual patients. Patients must return all unused medication and empty containers. These will be retained by study staff until collected by AstraZeneca authorized personnel.

The investigator must maintain accurate records accounting for the receipt of the investigational products (Astra Zeneca provides a copy of the investigational product shipping order for this purpose) and for the disposition of the material. This record keeping consists of a dispensing report including the identification of the person to whom the drug was dispensed, the quantity and date of dispensing and any unused drug returned on the CRFs.

The site should destroy unused study drug. Documentation indicating study drug was destroyed will be sent to AstraZeneca.

Certificates of delivery must be signed and dated. At the end of the trial, it will be necessary to reconcile delivery records with those of usage and returned stocks. Account must be given of any discrepancies.

#### Toxicities

The most common AEs associated with ZD6474 in the phase I and other monotherapy studies included rash, diarrhea and asymptomatic QTc prolongation. In Study ZD6474IL/0003 (the largest monotherapy ZD6474 study conducted as of this

date) the most frequent AEs for ZD6474 were diarrhea (55.4%), fatigue (36.1%), rash (27.7%), and nausea (24.1%). Approximately 10% of subjects who received ZD6474 had an adverse event of hypertension (HTN). The majority were Common Toxicity Criteria (CTC) grade 1 or 2. Three subjects developed CTC grade 3 HTN, and none were CTC grade 4. There were no serious adverse events (SAEs) of HTN. The median increase in systolic blood pressure for subjects who received ZD6474 was 10 mmHg; the median increase in diastolic blood pressure was 6 mmHg.

The cardiac events included a variety of terms without any apparent pattern. Respiratory events were primarily those that would be anticipated in subjects with advanced lung cancer. Three subjects receiving ZD6474 developed pulmonary embolism and 3 subjects developed interstitial lung disease, but cases were confounded by such factors as smoking, reduced mobility, infection, lung cancer progression and previous chemotherapy or radiation therapy. One subject in each arm developed a serious skin disorder. One subject who received ZD6474 developed a hematologic event, as did 2 subjects who received GEFITINIB. No subjects who received ZD6474 developed serious hepatotoxicity.

In Study 6474IL/0006, patients with advanced or metastatic NSCLC were enrolled after failure of prior platinum-based chemotherapy. Patients were randomized to treatment with a standard dose of Docetaxel and either placebo or 100 mg of ZD6474 or 300 mg of ZD6474. The most frequent AEs observed in this study were similar to those observed in prior trials for ZD6474 or reported for Docetaxel in the literature. The most common AEs and their frequencies as reported in the 300 mg ZD6474, 100 mg ZD6474 and placebo arms, respectively, were diarrhea (50.0%, 38.1%, 24.4%), fatigue (45.5%, 40.5%, 26.8%), neutropenia (31.8%, 26.2%, 19.5%) and nausea (29.5%, 26.2%, 19.5%). Rash was observed in 15.9%, 16.7% and 9.8% of patients in the three arms.

Gastrointestinal events (77.3%, 59.5%, 41.5%), and skin events (72.7%, 64.3%, 41.5%) were more common in the ZD6474-containing arms. For all arms, the majority of these events were common toxicity criteria (CTC) grade 1 and 2; however CTC grade 3/4 events were more prominent in the ZD6474 300 mg arm. Cardiac disorders occurred more frequently in ZD6474-containing arms (15.9%, 14.3%, 2.4%). The majority were CTC grade 1/2 and included a variety of terms, none ventricular. The frequency of respiratory events (50.0%, 57.1%, 46.3%) was similar in all arms. Neutropenia (31.8%, 26.2%, 19.5%) and related terms were more common in ZD6474-containing arms, but this did not result in an increase in infection. There was little difference in frequency of other hematologic events.

Approximately 10% of patients receiving ZD6474 developed an AE of hypertension. The majority of events were CTC grade 1 or 2, and no events were CTC grade 4. There were no serious adverse events (SAEs) of hypertension. The maximum median rise in both systolic and diastolic blood pressure was approximately 8 mm Hg in patients who received ZD6474 300 mg, and approximately 4 mm Hg in patients who received ZD6474 100 mg.

There were 12 subjects with confirmed QTc prolongation in Study ZD6474IL/0003. Of these, 6 occurred in the first 28 days, and 2 in the following 28 days. The remaining 4 occurred sporadically, with the longest time to occurrence 323 days. There were 3 events of CTC grade 1 reversible dizziness in subjects with a confirmed QTc prolongation occurring within the first 4 weeks. Subjects with dizziness had other events that might have caused dizziness and the events were not well correlated in time with the actual QTc prolongation. There were no other potentially relevant adverse events in subjects with confirmed QTc prolongation within the first 4 weeks, and no relevant adverse events in subjects whose first confirmed QTc prolongation occurred more than 4 weeks after randomization.

## 6.2 IRINOTECAN

### Availability/Product Description

Irinotecan hydrochloride trihydrate [CPT-11, (4S)-4,11-diethyl-4-hydroxy-9-[(4-piperidino- piperidino)carbonyloxy]-1H-pyrano[3',4':6,7]indolozino[1,2-b]quinoline-3,14(4H,12H) dinone hydrochloride trihydrate] (Camptosar®) is supplied in two forms: 2 ml vials containing 40 mg of drug and 5 ml vials containing 100 mg of drug. The drug is supplied in amber vials and appears as a pale yellow to yellow crystalline powder and pale yellow transparent solution when reconstituted. Irinotecan will be used from commercial stock.

### Drug Administration

Irinotecan will be diluted and administered as per institutional standard and infused intravenously as per institutional standard. It is strongly recommended that irinotecan be given over 90 minutes after cetuximab infusion.

### Storage and Stability

Irinotecan vials must be stored in a cool dry place, protected from light. Irinotecan is a relatively stable agent against heat and light but becomes slightly unstable against light in aqueous solution. Undiluted drug is stable for at least 3 years at room temperature. Irinotecan is stable for at least 24 hours in glass bottles or plastic bags when mixed with normal saline or 5% dextrose.

### Toxicities in Humans

Diarrhea and neutropenia are the major dose-limiting toxicities of irinotecan. Diarrhea can occur in two situations, within the first 24 hours and after 2-4 days. In the former situation, diarrhea may be associated with abdominal cramping and is thought to be mediated by non-competitive inhibition of acetyl cholinesterase activity by irinotecan. This is usually readily treatable with atropine, 0.25-1 mg, intravenously.

When diarrhea occurs late (after 2-4 days), and often after the second or third weekly dose of irinotecan, it can be a potentially serious event. In contrast to early diarrhea, delayed diarrhea appears to be secretory in nature and to result from abnormal intestinal ion transport. Anti-diarrheal agents, such as loperamide, diphenoxylate-atropine (Lomotil®), octreotide, scopolamine and bismuth are typically ineffective once grade IV diarrhea has occurred. The diarrhea usually lasts 5-7 days before resolving. Early recognition of diarrhea and prompt institution of an intensive and prolonged course of loperamide appears to be the most effective approach to this problem. It is recommended that patients take 4mg of loperamide immediately after their first loose bowel movement. Loperamide 2mg should be taken every 2 hours for a total of 12 hours if diarrhea persists. If no further loose bowel movements occur, therapy may be discontinued.

Myelosuppression is manifested primarily as leukopenia and neutropenia. Other toxicities include nausea, vomiting, alopecia and cumulative fatigue or asthenia. Instances of possible drug related hepatic toxicity have occurred, but are rare. Further descriptions are found in the package insert for irinotecan.

Several cases of interstitial pneumonitis have been reported, predominantly in the Japanese literature, with an incidence of 1.3%. Most reports have occurred in patients with primary lung tumors, where it is unclear whether the pulmonary toxicity was attributable to irinotecan, to progression of the underlying malignancy or to a combination effect. Clinically, this is manifested as worsening shortness of breath, fever and a reticulonodular infiltrate on CXR. Corticosteroids may be helpful in treatment. Hence, the exact mechanism by which pulmonary toxicity is mediated is unknown; however, a current belief is that it may represent an idiosyncratic reaction to the drug. No characteristic histologic correlates have been identified.

